## Abstract

**Introduction:**

In competitive sports, minor performance enhancements can significantly impact outcomes, driving athletes to utilize nutritional supplements, though many lack robust scientific evidence. Inorganic nitrate (NO₃⁻) stands out as a well‐supported ergogenic aid, particularly for high‐intensity activities, enhancing both performance metrics and psychological factors like perceived exertion. Wrestling, characterized by short, intense bursts of activity, necessitates efficient energy metabolism and recovery strategies. This protocol describes a trial to evaluate the acute effects of vitamin C‐enriched beetroot supplementation on the performance of semi‐professional wrestlers, assessed through upper and lower body Wingate tests.

**Method:**

This study will conduct a double‐blind, randomized, placebo‐controlled crossover trial involving 28 semi‐professional wrestlers. Participants will be assigned to receive either a beetroot juice containing 8.4 mmol of nitrate and 90 mg of vitamin C or a placebo. Randomization will be facilitated through a web‐based tool, ensuring blinding with placebo drinks. The primary outcome will be maximal anaerobic power, while secondary outcomes will include mean anaerobic power, fatigue index, time to exhaustion, and metabolic markers associated with muscle damage, such as creatine kinase and lactate dehydrogenase. The trial is registered at IRCT20240407061440N1.

**Results:**

Not applicable (study protocol).

**Conclusion:**

This protocol describes a rigorous trial to evaluate potential ergogenic and recovery benefits of vitamin C‐enriched beetroot in wrestling‐specific anaerobic performance, addressing gaps in multi‐muscle group testing.

AbbreviationsCKcreatine kinaseCONSORTconsolidated standards of reporting trialsLDHlactate dehydrogenaseNOnitric oxideNO₃⁻inorganic nitrateRPEratings of perceived exertionSPIRITstandard protocol items: recommendations for interventional trialsWAnTwingate anaerobic test

## Introduction

1

In competitive sports, even marginal enhancements in performance can profoundly influence competition outcomes, prompting athletes to increasingly rely on nutritional supplements. However, many such supplements lack robust scientific validation for their efficacy. To bridge this evidence gap, the International Olympic Committee has developed a categorization system for nutritional supplements, evaluating them based on the strength of supporting research for athletic performance benefits [1].

Among these, inorganic nitrate (NO₃⁻) has emerged as a promising ergogenic aid, particularly for high‐intensity sports, with evidence from meta‐analyzes demonstrating improvements in aerobic and anaerobic performance among recreationally active individuals [2, 3]. Recent studies, further confirm that beetroot‐derived nitrate supplementation enhances muscle endurance, time to exhaustion, and power output during high‐intensity efforts, while also reducing oxygen consumption and perceived exertion [4, 5, 6, 7, 8, 9, 10, 11]. These benefits extend to reductions in systemic blood pressure and improved efficiency in submaximal exercise.

Beyond physiological effects on skeletal muscle, psychological factors such as mood and ratings of perceived exertion (RPE) play a critical role in exercise performance [12]. Excessive use of ergogenic supplements can elevate subjective tension, a state of internal readiness for challenging tasks [13, 14]. Consequently, consuming nitrate‐rich sources like beetroot or beetroot juice prior to competition may lead significant performance gains [15], especially in anaerobic‐dominant activities.

Ascorbic acid (vitamin C) in beetroot juice augments nitric oxide (NO) bioavailability by promoting the reduction of nitrate to nitrite [16, 17], and acts as a redox‐active cofactor [16, 17, 18], modulates redox‐sensitive signaling pathways [19], enhances endothelial function [20], and may influence mitochondrial and metabolic efficiency during high‐intensity exercise. In combination with polyphenols, it optimizes nitrate conversion to NO while limiting unwanted nitrogen oxide byproducts [18]. Recent evidence suggests potential synergy between vitamin C and nitrate, enhancing urinary nitrate excretion and possibly supporting recovery, though data on acute combined effects in anaerobic performance remain limited [21]. However, the evidence for combined nitrate + vitamin C supplementation in high‐intensity anaerobic exercise remains limited and mixed. While some studies indicate improved NO bioavailability and reduced oxidative stress with acute co‐ingestion, broader reviews on antioxidant supplementation (including high‐dose vitamin C) during intense exercise show inconsistent or neutral effects on performance and recovery, potentially due to interference with adaptive signaling pathways [22, 23].

Wrestling exemplifies a sport reliant on anaerobic energy pathways, with high‐intensity bursts lasting 6 to 60 s primarily driven by glycolytic metabolism [24]. While acute beetroot supplementation has been extensively studied for its impact on upper and lower body Wingate Anaerobic Test (WAnT) outcomes, gaps persist in examining repeated, alternating upper‐ and lower‐body WAnT performances, a protocol that better mimics wrestling's demands for multi‐muscle group engagement [25]. Prior research has focused on consecutive efforts within the same body region, overlooking the explosive, sequential involvement of both upper and lower body typical in combat sports.

Furthermore, evidence on beetroot's role in attenuating muscle damage is mixed. A 2024 study showed beetroot consumption reduces creatine kinase (CK) and lactate dehydrogenase (LDH) levels, offering protection against damage [26]. with similar findings in sports like fencing [27]. However, these benefits were absent in soccer or marathon running [28, 29], likely due to variations in training status, exercise modality, supplementation protocols, and intermittent demands. Given these inconsistencies and promising results in high‐intensity contexts, there is a clear need for a controlled interventional study that replicates wrestling‐specific conditions, emphasizing dual‐muscle group involvement.

### Objectives

1.1

The primary objective is to evaluate the acute effects of vitamin C‐enriched beetroot supplementation on maximal anaerobic power during upper and lower body Wingate tests in semi‐professional wrestlers.

Secondary objectives include assessing impacts on mean anaerobic power, fatigue index, time to peak power, and muscle damage markers (creatine kinase, lactate dehydrogenase, blood glucose), as well as ratings of perceived exertion.

### Hypotheses

1.2

We hypothesize that acute supplementation with vitamin C‐enriched beetroot juice (8.4 mmol nitrate and 90 mg vitamin C) may enhance anaerobic performance metrics and reduce muscle damage compared to placebo, potentially driven by increased nitric oxide production and antioxidant effects. These hypotheses will be tested in the proposed trial.

## Methods and Analysis

2

The protocol for the present double‐blind, randomized, placebo‐controlled, crossover study is meticulously aligned with the Standard Protocol Items: Recommendations for Interventional Trials (SPIRIT) guidelines [30] for trial protocols and the Guidelines for reporting of statistics for clinical research in urology [31] (Figure 1). Ethical approval has been obtained from the Medical Ethics Committee of Mashhad University of Medical Sciences (IR.MUMS.MEDICAL.REC.1403.011), and the study has been officially registered with the Iranian Registry of Clinical Trials (IRCT20240407061440N1) with a registration date of June 7, 2024.

**Figure 1 hsr272218-fig-0001:**
[figure not shown]
CONSORT 2010 Flow Diagram for participant enrollment, allocation, follow‐up, and analysis in this crossover trial.

### Protocol Version and Trial Status

2.1

This protocol is version 1.0, dated 1 August 2025. Recruitment has not yet commenced and is planned to begin in September 2025, with completion expected by December 2025.

### Study Design and Setting

2.2

This double‐blind, crossover study will involve 28 semi‐professional wrestlers, who will receive both vitamin C‐enriched beetroot juice and placebo in random order, separated by a 14‐day washout period. Participants will be selected by their respective wrestling coaches and will be randomly assigned to receive either a 240 mL dose of a vitamin C‐enriched beetroot juice or a placebo. The beetroot juice will contain 8.4 mmol of nitrate derived from beetroot powder produced through a freeze‐drying process, along with natural mineral nitrate (3.2%), phenolic compounds, ascorbic acid, carotenoids, and betalains. Additionally, the beetroot juice for the intervention group will include 90 mg of vitamin C, with no additives or preservatives. The 90 mg dose of vitamin C was chosen based on pharmacokinetic data showing that intakes in the 75–100 mg range achieve near‐maximal plasma saturation in healthy adults [32], thereby supporting nitrate‐related nitric oxide processes without entering high‐dose pharmacological ranges that could potentially interfere with adaptive signaling.

The following inclusion criteria will be adopted:
Healthy semi‐professional wrestlers aged 18–24 years.Interested in participating in the project and following the study protocol.Having more than 2 years of wrestling experience.Not being an elite athlete.Not performing any type of physical exercise 72 h before each session.The exclusion criteria will be as follows:Smoking or consuming alcohol.Consuming caffeine‐containing drinks 24 h before the start of the intervention.Having a history of cardiovascular, lung, metabolic, neurologic, or orthopedic disorders that could limit cycle ergometry performance.Utilizing nitrate‐containing pharmaceuticals, such as nitroglycerin or isosorbide.Taking nutritional supplements in the 6 months prior to the study onset.Using mouthwash or oral antiseptic within the past 4 weeks.Taking any herbal medicine.Having an allergy to red beets.

Participants will be required to abstain from caffeine for 24 h (per exclusion criteria), ensure at least 7 h of sleep, and avoid cognitively demanding tasks for 12 h before each session to control potential confounders. The application of oral antiseptics has the potential to inhibit elevated blood NO₂⁻ concentrations following the consumption of NO₃⁻ due to their bactericidal properties targeting oral bacteria. Consequently, participants will be instructed to avoid brushing their teeth, using mouthwash, chewing gum, or consuming sweets that may contain bactericidal agents like chlorhexidine or xylitol for a period of 24 h before the testing sessions.

Participants will be instructed to maintain a fixed diet of 60% carbohydrate, 30% fat, and 10% protein, avoiding high‐fat foods for 48 h prior to each test session. In addition, they will be given a list of NO₃⁻‐rich vegetables (including beets, celery, arugula, lettuce, spinach, turnips, endives, chives, parsley, and cabbage) to avoid the day before the study begins. A 72‐h food recall will be conducted to ensure adherence to a standardized diet, minimizing dietary confounders. Supplements will be administered 3 h before Wingate tests to optimize nitrate [33], vitamin C [32], and polyphenol bioavailability [34], aligning with peak plasma concentrations. The restriction on the intake of NO₃⁻‐rich foods 48 h prior to each session will ensure that participants in the placebo group are sufficiently depleted of NO₃⁻ (Figure 2).

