### Control Group

2.5

Participants assigned to the control group will receive a beverage that visually resembles the beetroot supplement. The placebo drink will consist of a neutral solution containing 0.4 mg/mL citric acid, 0.2 mg/mL food coloring, and 0.25 g/mL sugar, formulated to match the appearance, taste, and texture of the beetroot juice without containing nitrates, vitamin C, or polyphenols.

The beetroot juice intervention will be similarly supplemented with 0.25 g/mL sugar to ensure identical sweetness and caloric content, maintaining effective blinding. Both drinks (240 mL each) will be prepared by a third‐party supplier to ensure consistency and double‐blinding.

After a 3‐h interval, a baseline blood sample will be collected from the subjects. The Wingate upper body functional test will be performed immediately thereafter, followed by the Wingate lower body test, which will be conducted 1 to 4 min later. Blood samples will be collected immediately after the Wingate lower body test and again 24 h later. Additionally, participants will complete the RPE questionnaire during both test sessions.

Given that the half‐life of nitrate is approximately 5 to 8 h, a 14‐day washout period is considered sufficient to effectively reduce any residual effects that may arise from prior nitrate supplementation [35]. Since participants will serve as their own controls, sessions will be scheduled at the same time each day to maintain consistency.

The study's design is illustrated in Figure 3. Throughout the experimental phase, each participant will complete two visits to the laboratory.

Studies have also demonstrated that the performance of high‐intensity lower body exercises is not significantly compromised by prior upper body activity. As such, it will be feasible to conduct lower body testing and training either preceding or following upper body sessions without negatively affecting the power output of the lower body [36]. In this study, we will administer the upper body Wingate test, followed by the lower body Wingate test. This sequential testing design will enable a thorough assessment of the effects of the two supplements on performance across different muscle groups.

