### Study Assessments

2.16

Participants will undergo initial and concluding evaluations encompassing several assessments. These will include a comprehensive questionnaire gathering general information, the International Physical Activity Questionnaire, a 72‐h food recall prior to testing, and administration of the Rate of Perceived Exertion (RPE) Scale during upper and lower body Wingate tests using the Borg scale [39]. Additionally, participants will receive a detailed list of foods rich in nitrates and will be instructed to abstain from consuming these items throughout the study duration.

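### The pre-test diet is set as energy percentages, with no amount and no stated instruction to repeat visit-1 intake before visit 2, so avoidable within-person variance can enter the crossover comparison

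*Protocol article*

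**What the plan says.** Section 2.2 (Study Design and Setting) gives the dietary standard: "Participants will be instructed to maintain a fixed diet of 60% carbohydrate, 30% fat, and 10% protein". The same sentence bars high-fat foods and attaches the window "48 h prior to each test session". The section then says that a 72-h "food recall will be conducted to ensure adherence to a standardized diet, minimizing dietary confounders". Section 2.3 has staff confirm adherence to pre-test instructions on arrival at each visit. Section 2.16 lists the recall within the initial and concluding evaluations, which reads as one per visit. Section 2.17 has trained staff administer it to verify dietary adherence.

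On matching the two visits, Section 2.5 (Control Group) says that participants act as their own controls and that "sessions will be scheduled at the same time each day to maintain consistency". Section 2.2 also sets rules on exercise, caffeine, sleep, cognitively demanding tasks, oral antiseptics and nitrate-rich foods. Both drinks contain 0.25 g/mL added sugar in 240 mL (Section 2.5).

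No section states an energy intake, a carbohydrate amount or a supplied meal. None states an instruction to repeat visit-1 intake, or a rule on food between the drink and the 3-h sample.

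**The concern.** A percentage split fixes the shape of the diet but not its quantity. A participant who eats little before one visit and freely before the other can meet 60/30/10 both times. The adherence checks inherit this gap: a recall judged against percentages has no basis for flagging a large difference in amount between the two visits.

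This matters because the planned comparison is within person (paired tests, Section 2.21), so its precision depends on how alike a participant's two sessions are apart from the drink. The protocol itself describes wrestling bursts as driven by glycolytic metabolism (Introduction) and the Wingate test as a measure of glycolytic capacity (Discussion). Blood glucose is a secondary outcome (Section 2.7). Carbohydrate supply is therefore a plausible source of session-to-session variation in what is measured, and the crossover gives up some of its advantage if that supply is left loose.

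**Working it through.** **1. What the percentage rule allows.** Carbohydrate in grams = 0.60 × kcal ÷ 4. The energy intakes are assumptions; the document gives none.

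| Assumed kcal/day | Carbohydrate at 60% |
|---|---|
| 1,800 | 0.60 × 1,800 ÷ 4 = 270 g |
| 2,000 | 0.60 × 2,000 ÷ 4 = 300 g |
| 3,500 | 0.60 × 3,500 ÷ 4 = 525 g |

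All three satisfy the rule, and the extremes differ by 525 ÷ 270 = 1.94.

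**2. What the drinks contribute.** Added sugar is 0.25 g/mL × 240 mL = 60 g in each drink. The drinks create no planned difference in added sugar. They also do not equalise the preceding 48 to 72 h.

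**3. Effect on the confidence interval.** Assume a within-person SD of 5% for peak power at a session, and that unmatched diet adds an independent SD of 2% to 3%. The variance of the paired difference scales with the per-session variance, so the ratios are:

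- diet SD 2%: (25 + 4) ÷ 25 = 1.16; width ratio √1.16 = 1.08
- diet SD 3%: (25 + 9) ÷ 25 = 1.36; width ratio √1.36 = 1.17

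The interval is 8% to 17% wider. All three SDs are assumptions.

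**4. Effect on power for the planning difference.** The plan's own figure first. Section 2.8 gives 508.14 (SD 117.55) W and 607.36 (SD 112.28) W, a difference of 99.22 W. Its formula yields (117.55² + 112.28²)(1.960 + 0.842)² ÷ 99.22² = 21.07, rounded up to the stated 22. These inputs are for mean power, so they serve here only as a scale.

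For a paired test, the SD of differences is √(117.55² + 112.28² − 2r × 117.55 × 112.28). At an assumed within-person correlation r = 0.5 this is 115.0 W. With 22 completers and two-sided 5%:

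| Increase in SD of differences (assumed) | Power for 99.22 W | Difference detectable at 80% power |
|---|---|---|
| none | 97% | 72.0 W |
| 10% | 94% | 79.2 W |
| 25% | 87% | 90.1 W |
| 50% | 73% | 108.1 W |

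At r = 0.8, power for 99.22 W stays at 98% or more in every row. An 8% to 17% increase lies between the first and third rows. The loss is small for an effect as large as the planning one. It counts for more if the true effect is smaller.

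**The case against.** **Control is weak, not absent.** The diet is called fixed and standardised, a recall and an arrival check are planned, and high-fat and nitrate-rich foods are restricted before sessions. A participant who halves or doubles his intake is hardly keeping a fixed diet in the ordinary sense. This stands in part: the intention is clear, but the only stated standard is a ratio, which cannot show the difference.

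**The article is condensed.** Diet sheets and an instruction to repeat intake may be in the full protocol. This also stands. One can say only that no repetition is stated, not that none will happen.

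**Randomised order and blinding.** These stand fully. Dietary differences between visits are not expected to favour either drink.

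**Stronger readings that the document does not support.** A reader of Section 2.5 might infer that time of day is the only condition held alike at both visits. The exercise, caffeine, sleep, cognitive-task, oral-antiseptic, high-fat and nitrate rules show otherwise.

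A reader might also start from the dose rationale in Section 2.2, "pharmacokinetic data showing that intakes in the 75–100 mg range" giving near-maximal plasma levels. He could infer that unrestricted dietary vitamin C shrinks the vitamin C contrast to almost nothing, while nitrate restriction "will ensure that participants in the placebo group are sufficiently depleted of NO₃". That goes too far:

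- The objective concerns the combined drink against placebo.
- The Discussion gives vitamin C a role in the mouth and gut when taken together with nitrate, which prior plasma saturation does not remove.
- Section 2.2 excludes supplement use in the preceding 6 months.
- Section 3.1 already concedes that vitamin C's contribution cannot be isolated, that its status is unmeasured, and that the recall is only descriptive on this.

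**Conclusion.** The point holds as a minor design weakness. As described, the diet rule lets energy and carbohydrate intake differ between a participant's two sessions without breaching it, and the planned recall is not used to match them. The consequence is lost precision for Wingate power and blood glucose. It is not bias in the treatment comparison.

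The document does not allow the size to be estimated. The 8% to 17% wider interval follows only if the within-person SD is 5% and diet adds an independent 2% to 3%. For the planning difference of 99.22 W, power with 22 completers would probably remain high at a within-person correlation of 0.5 or more, unless diet noise were much larger than that. The sample size is therefore not called into question here, and no restriction on vitamin C-rich foods follows from this point.

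**What to change.** At the end of visit 1, give each participant a copy of his 72-h recall. Instruct him to eat the same foods in the same amounts over the 72 h before visit 2, leaving out any item that breached the existing dietary rules. Record anything taken between the drink and the 3-h sample at visit 1 and have it repeated at visit 2. Compare the second recall with the first, in amounts as well as percentages, and note departures. As an option, summarise recalled vitamin C intake by treatment visit, for description only.

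The cost is a few lines of protocol wording, a copy of a form already collected, and some effort from participants. Section 2.1 says that recruitment had not begun at version 1.0. If that is still so, the change can apply to everyone.

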**Figure 2 hsr272218-fig-0002:**
[figure not shown]
Overview of the double‐blind, randomized, placebo‐controlled crossover trial design, including intervention, washout, and outcome assessments.

### Participant Timeline

2.3

Participants will attend two laboratory visits, separated by a 14‐day washout period. Each visit will follow this schedule:
T = 0 h: Arrival, confirmation of adherence to pre‐test instructions, supplement administration (beetroot or placebo).T = 3 h: Baseline blood sample collection, anthropometric measurements.T = 3+ hours: Upper body Wingate test, followed by lower body Wingate test (1–4 min later), with RPE assessment during tests.Immediate post‐test: Blood sample collection.T = 27 h (24 h post‐test): Follow‐up blood sample (Figure 3).

**Figure 3 hsr272218-fig-0003:**
[figure not shown]
Detailed participant timeline showing timing of supplementation, blood sampling and Wingate tests (upper then lower body) across the two sessions separated by 14‐day washout.

### Intervention Group

2.4

Participants in the intervention group will be administered a single sports drink containing a blend of red beets and vitamin C (8.4 mmol of nitrate and 90 mg of vitamin C). After a 3‐h interval, baseline blood samples will be collected from the subjects. The Wingate upper body functional test will be conducted immediately thereafter, followed by the Wingate lower body test, which will occur 1 to 4 min later. Blood samples will be obtained immediately following the Wingate lower body test and again 24 h later. Additionally, participants will complete the RPE questionnaire during both testing sessions.

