### Secondary Outcomes

2.7

Secondary outcome measures will include anaerobic mean power, anaerobic minimum power, time to peak power, fatigue index, and various indicators to evaluate muscle damage, including levels of creatine kinase, lactate dehydrogenase, and blood glucose.

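### The blood sample called baseline is drawn 3 h after the drink, glucose is classed as a muscle-damage marker, and the stated exercise restriction does not reach the 24-h CK/LDH sample

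*Protocol article*

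**What the plan says.** The Participant Timeline (2.3) puts arrival and the drink at T = 0 h and then has "T = 3 h: Baseline blood sample collection, anthropometric measurements". The two arm descriptions agree: "After a 3‐h interval, baseline blood samples will be collected from the subjects" in 2.4 and "After a 3‐h interval, a baseline blood sample will be collected from the subjects" in 2.5. The Wingate tests follow at once. Further blood is taken straight after the lower body test and again 24 h later (T = 27 h).

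Section 2.7 lists among the secondary outcomes "various indicators to evaluate muscle damage, including levels of creatine kinase, lactate dehydrogenase, and blood glucose", and the Objectives (1.1) group the three in the same way. On the drinks, 2.5 gives the placebo 0.25 g/mL of sugar in 240 mL and adds: "The beetroot juice intervention will be similarly supplemented with 0.25 g/mL sugar".

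The only exercise restriction is an inclusion criterion in 2.2: "Not performing any type of physical exercise 72 h before each session".

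**The concern.** Baseline normally means before treatment. Here it means before exercise but after the supplement. Section 2.2 chose the 3-h interval so that testing falls at peak plasma concentrations, so this sample is taken at the intended peak of exposure. An analyst who takes the label at face value may compute change from it or adjust for it, and would then subtract part of the effect under study. Nor can the trial show that a participant's CK and LDH were at the same level before the two drinks.

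Two related matters affect the same markers. A glucose difference could be reported as evidence on muscle damage, although the measurement follows a sugar load. And the 24-h CK and LDH values, which are meant to reflect damage from the Wingate tests, are open to the effect of any training done in the meantime. The hypotheses (1.2) include reduced muscle damage, so these markers carry a stated claim of the trial.

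**Working it through.** **Plan's own figure.** The document gives no computed figure for the blood markers. Its one computed figure, the sample size in 2.8, rests on power output: (117.55² + 112.28²) × (1.96 + 0.8416)² / 99.22² = 21.07, rounded up to 22, as stated. Nothing below changes it.

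**Sampling times against dosing time (2.3, 2.4, 2.5).**
- Drink: T = 0 h.
- Blood: T = 3 h, immediately post-test, T = 27 h. That is 3 samples per period and 3 × 2 = 6 per participant.
- Samples before the drink: 0 of 6. The initial and concluding evaluations in 2.16 list questionnaires, a food recall and perceived exertion, but no blood.

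**Exposure at the 3-h draw.** Section 2.5 gives a nitrate half-life of about 5 to 8 h. With simple first-order decay from T = 0, ignoring absorption (an assumption), the share remaining at 3 h is 0.5^(3/5) = 66% to 0.5^(3/8) = 77%.

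**What a change score would lose.** Let the drink effect on a marker at a later sample be δ and the effect already present at 3 h be f × δ. The treatment contrast in change from the 3-h value is δ − fδ = (1 − f)δ. The document gives no value for f. Over an assumed range:
- f = 0: 100% of δ is recovered
- f = 0.1: 90%
- f = 0.25: 75%
- f = 0.5: 50%

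Using the 3-h value as a covariate with slope b gives (1 − bf)δ, which for b between 0 and 1 is the same loss in weaker form. A direct comparison of the later values returns δ whatever f is.

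**Glucose.** Added sugar before every glucose sample labelled baseline: 240 mL × 0.25 g/mL = 60 g, in either drink. The Discussion (section 3), where it explains what the damage markers can and cannot show, names only CK and LDH. The Abstract also names those two, but as examples, so it is weaker evidence.

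**Exercise restriction.** Hours covered before the session: 72. Hours covered between the tests and the last sample: 0 of 24. The 24-h draw cannot sensibly count as a session in its own right, because a 72-h ban before it would forbid the Wingate tests done 24 h earlier. Sections 2.3 and 2.5 also count only two laboratory visits.

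**The case against.** The strongest reply is that the 3-h draw is a proper pre-exercise value. CK and LDH are there to show the response to the Wingate tests, the sample is taken just before them, and the three sections agree, so nothing is contradictory. This stands. The fault is in the label and in what the label invites, not in taking a sample at that time.

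A reader might infer that the treatment comparison on the markers is biased. The document does not support that. The Statistical Analysis section (2.21) plans within-subject comparisons of the two drinks and nowhere says that the markers will be analysed as change. Order is randomised 1:1 (2.13.1), so comparing post-test or 24-h values between drinks is unbiased without a pre-dose sample. Whether CK or LDH moves within 3 h of the drink cannot be settled from the text.

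A reader might also infer that the first draw should be moved to T = 0 h. That would cost the only pre-exercise value and leave the post-test change mixing exercise with 3 h and a sugar drink, which is worst for glucose. Nor can a large precision gain from a pre-dose covariate be assumed, because the paired comparison already removes stable differences between participants.

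On glucose, a reader might infer that the two drinks differ in sugar load. The document neither shows nor excludes this: the added sugar is equal, identical caloric content is the stated aim, and the sugar in the beetroot itself is not given.

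On training, the article is condensed, and an instruction for the 24 h after the tests may exist in a fuller protocol. It is also true that such training, under blinding, mainly adds noise and need not favour either drink. What remains is that the one restriction the article states has a fixed window, and that window ends before the sample most exposed to training.

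**Conclusion.** The point holds in a limited form. The sample called baseline is post-supplement and pre-exercise, and no pre-dose CK, LDH or glucose value is planned. Using it as a pre-treatment baseline would remove a share f of any drink effect. That share is unknown; under the assumed range of 0 to 0.5, the loss runs from nothing to half. Glucose after 60 g of added sugar is not evidence on muscle damage, and its place in that set should be corrected. The stated exercise restriction leaves all 24 h before the last sample uncovered, which can add avoidable within-subject noise to CK and LDH. The size of that noise cannot be computed from the document.

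The primary outcome, maximal anaerobic power, and the sample size are untouched. The Limitations (3.1) mention missing baseline vitamin C status and redox markers but not the missing pre-dose CK, LDH and glucose.

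**What to change.** Section 2.1 states that recruitment had not begun at this version, so these changes can be made in advance.

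- In 2.3, 2.4 and 2.5, rename the 3-h sample as pre-exercise, post-supplement. In 2.21, state that CK and LDH are compared between drinks on the post-test and 24-h values, and that the 3-h value is not used as a pre-treatment baseline. Cost: wording only.
- Extend the existing no-exercise instruction through the 24-h sample at both visits. Cost: one more training day lost per period.
- In 1.1 and 2.7, take glucose out of the muscle-damage set and report it as a metabolic outcome. Cost: none.
- Optionally, add a draw on arrival before the drink, to show whether the two visits start level. This would be one additional draw per period, kept alongside the 3-h sample and not in place of it. If it is not added, list the missing pre-dose values in 3.1.
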